#### Exclusion criteria

1. < 18 years of age

2. Persistent ST elevation on the presenting ECG

3. Intention to treat with an urgent reperfusion strategy (thrombolysis or primary percutaneous coronary intervention)Percutaneous coronary intervention within previous 3 months

4. Previous coronary artery bypass grafting

5. ECG showing paced rhythm

6. Cardiogenic shock (as defined in the Trial Manual)

7. Any serious co-morbidity which makes it unlikely that the patient will complete trial procedures and follow-up

8. Treatment or under active follow-up for rheumatoid arthritis, other connective tissue diseases or inflammatory bowel disease

9. End stage renal disease or a Creatinine > 220 μmol/L

10. Pregnancy or suspected pregnancy (any potential female participant of child bearing age will need a negative pregnancy test prior to study entry)

11. Eosinophilia

12. Anti-TNF biologies

13. Active infection

14. Malignancy

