### Interleukin 1 receptor antagonist (IL-1ra)

There are two agonistic cytokines (IL-1α and IL-1β) that signal via the Type 1 IL-1 receptor (IL-1R1) and a specific Interleukin-1 receptor antagonist (IL-1ra), (the only known naturally occurring cytokine antagonist) that inhibits IL-1 actions by binding to the IL-1R1, blocking the receptor and preventing IL-1 from binding thereby preventing receptor signalling [7].

IL-1ra is available for the treatment of a number of inflammatory conditions as a recombinant, non-glycosylated, N-terminal methionine added protein (Kineret/Anakinra, Amgen). Although less successful than anti-TNF therapies in rheumatoid arthritis (RA), there appears to be considerable benefit in the management of Juvenile arthritis (Still's disease), and it is the treatment of choice in the rare autoinflammatory illnesses typified by Muckle-Wells syndrome. From all of the indications in which IL-1ra has been used it has emerged that IL-1ra is a very safe form of treatment and appears to be devoid of the side-effect of re-activation of infectious illness seen with anti-TNF therapies. The only problems encountered are mild, reversible injection site reactions and neutropaenia in <1% of patients after a month or more of treatment.

Dosing with IL-1ra is simple. A single, daily, subcutaneous 100 mg injection of IL-1ra is the standard dose of IL-1ra for all individuals with normal renal function. In RA this causes a 35% reduction in CRP after approximately 1 week of treatment. Higher doses do not achieve any greater reduction in CRP of relief of RA symptoms. Single daily dosing schedules are used in the sucessful treatment of Juvenile arthritis and Muckle-Wells. The half-life of IL-1ra is 4–6 hours with maximum absorption from an s.c. injection at 3–7 hours. (Data on file supplied by Amgen).

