### Study treatment

Eligible patients will be randomised in equal proportions between IL-1ra and placebo, receiving either a once daily, subcutaneous (s.c). injection of IL-1ra (dose 100 mg per 24 h) for 14 days, or a daily s.c. injection of placebo for 14 days. The hospital pharmacist will issue the relevant drug package. (Please see appendices for pharmacy information).

The study drug and placebo will be provided by Amgen Inc in its commercially available recombinant form which is in clinical use for the treatment of arthritic conditions. The study drug and placebo will be relabelled by Amgen, in collaboration with CTEU according to MHRA guidelines.

The first dose of IL-1ra will be given within 24 h +2 h of the positive Troponin. Injections will be given at a standardised time (24 ± 2 h after the previous dose), immediately after blood sampling. IL-1ra or placebo will administered to the patient by the research nurse while the patient is in hospital. During the hospital stay, the patient will be taught to self-administer the injection by the research nurse and on discharge will continue at home. This has proven possible in other ACS trials that required self injection of subcutaneous heparin [36]. Full written guidance on self injection will also be provided to patients. If self injection is found not to be possible in an individual patient for unexpected reasons, an alternative method will be sought (e.g. district nurse, or attending the hospital) to try and maintain full compliance with scheduled study drug regimen after discharge. Patients will also be asked to complete a daily injection diary. All personnel will be blinded to the identity of the syringe contents.

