### Study related investigations and follow-up

Patients will have blood taken every day for seven days for hsCRP (baseline and days 1–7, 14 and 30), Troponin (baseline and days 1–7 and 14), full blood count (baseline, days 7 and 14), creatinine, electrolytes, liver function tests (baseline, days 1–7 and 14), Interleukin-6 and von Willebrand factor (baseline, days 1–3,14,30). Blood will be taken prior to administration of either IL-1ra or placebo. A summary of samples and study related procedures to be undertaken is shown in Table 1. If the patient is discharged before the seventh day, they will be required to attend clinic to have the remaining blood samples taken.

**Table 1 T1:** Study procedures

Procedure	Baseline	Days 1 – 7	Days 8–13	Day 14	Day 30 (end of study)
Clinical evaluation	√	√		√	√
Informed consent	√				
Randomisation	√				
ECG	√	√		√	
Study drug given		√	√	√	
Full blood count	√	√		√	
Creatinine, electrolytes, eGFR	√	√		√	
Troponin	√	√		√	
hsCRP	√	√		√	√
Liver function tests	√			√	
IL-6, vWF	√	√		√	√
Post discharge follow up visit				√	√
Samples for DNA & RNA	√				√
Cardiac magnetic resonance scan (1)		√			√
ST segment monitoring (2)		√			
Forearm endothelial study (3)		√		√	

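### The protocol's stated basis for the fixed daily dose covers normal renal function only, but the same dose goes to every eligible patient with creatinine up to 220 μmol/L

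*Protocol article*

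**What the plan says.** Three places in the protocol article bear on this point.

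- **Background, Interleukin 1 receptor antagonist (IL-1ra).** The dose is introduced as follows: "A single, daily, subcutaneous 100 mg injection of IL-1ra is the standard dose of IL-1ra for all individuals with normal renal function". The renal qualifier is the authors' own. The section says nothing about the dose in people whose renal function is not normal.
- **Study treatment.** "Eligible patients will be randomised in equal proportions between IL-1ra and placebo", and the active arm receives a once-daily "injection of IL-1ra (dose 100 mg per 24 h) for 14 days". No renal condition is attached, and the interval between injections is fixed at 24 ± 2 h.
- **Exclusion criteria, item 9.** The renal limit is "End stage renal disease or a Creatinine > 220 μmol/L".

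Two further items are relevant. Exclusion 7 removes "Any serious co-morbidity which makes it unlikely that the patient will complete trial procedures and follow-up". Table 1 lists "Creatinine, electrolytes, eGFR" at baseline, days 1–7 and day 14, but the text available does not tie these measurements to eligibility or dosing.

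**The concern.** The protocol treats renal function as relevant in two places and draws the line differently in each. The dose rationale stops at normal function. The eligibility rule stops at end stage disease or a creatinine above 220 μmol/L. Patients between those lines are eligible and, if allocated to IL-1ra, receive the full fixed regimen for 14 days, although the document's supporting statement does not extend to them.

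What is at stake is the justification for exposing these patients. Drug related serious adverse reactions lists serious infection (1.8% on IL-1ra, 0.7% on placebo) and neutropenia (2.4% and 0.4%). An ethics committee or data monitoring committee would expect the stated basis for the dose to reach everyone who may be given it.

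**Working it through.** The plan gives no figure to reproduce on this point. The check is a comparison of text, followed by a conversion that shows how far the eligible range extends.

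**Step 1. Compare the populations.**

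| Source | Renal population covered |
|---|---|
| Dose rationale (Background) | Normal renal function |
| Regimen (Study treatment) | All eligible patients allocated to IL-1ra |
| Eligibility (exclusion 9) | Everyone except end stage disease or creatinine > 220 μmol/L |

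The second and third rows agree with each other. Both are wider than the first, and the difference is every eligible patient with reduced function.

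**Step 2. See whether another provision closes the gap.** Exclusion 7 acts only when co-morbidity makes completion unlikely, so it is not a renal limit. The scheduled creatinine and eGFR measurements have no stated consequence for entry or dosing. The appendix text available on labelling and storage contains no renal provision.

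**Step 3. Convert the limit into estimated function.** The creatinine limit comes from exclusion 9. The exclusions set a lower age limit ("< 18 years of age") and no upper one. The equations, the ages 40 to 80 and the weights 60 to 90 kg are assumptions and are not in the documents.

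Unit conversion: 220 / 88.4 = 2.49 mg/dL.

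Worked example, man aged 65:

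- MDRD: 175 × 2.489^(−1.154) × 65^(−0.203) = 26.2
- CKD-EPI 2009: 141 × (2.489/0.9)^(−1.209) × 0.993^65 = 26.1
- CKD-EPI 2021: 142 × (2.489/0.9)^(−1.2) × 0.9938^65 = 28.0
- Cockcroft-Gault at 70 kg: (140 − 65) × 70 × 1.23 / 220 = 29.4 mL/min

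For women, MDRD is multiplied by 0.742. CKD-EPI uses 0.7 in place of 0.9 and a multiplier of 1.018 (2009) or 1.012 (2021). Cockcroft-Gault uses 1.04 in place of 1.23.

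Estimated function at 220 μmol/L:

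| Equation | Men, 40–80 | Women, 40–80 | Man, 65 | Woman, 65 |
|---|---|---|---|---|
| MDRD (mL/min/1.73 m²) | 25.1–28.9 | 18.6–21.4 | 26.2 | 19.4 |
| CKD-EPI 2009 (mL/min/1.73 m²) | 23.5–31.1 | 17.7–23.4 | 26.1 | 19.6 |
| CKD-EPI 2021 (mL/min/1.73 m²) | 25.5–32.7 | 19.1–24.5 | 28.0 | 20.9 |
| Cockcroft-Gault, 60–90 kg (mL/min) | 20.1–50.3 | 17.0–42.5 | 29.4 (70 kg) | 24.8 (70 kg) |

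Across MDRD and both CKD-EPI versions the range is 17.7 to 32.7. For Cockcroft-Gault it is 17.0 to 50.3. Under every equation a patient at the limit is far from normal function. These figures describe the edge of the eligible range, not the typical recruit.

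**The case against.** **It is a silence, not a contradiction.** The Background calls the dose standard for people with normal function. It does not call it unsuitable in others, so a reader who infers that the protocol forbids its own regimen goes too far. This stands. What remains is that the dose is given to patients whom the stated rationale does not reach.

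**The answer may lie elsewhere.** Study treatment refers to appendices for pharmacy information, the Labelling item refers to the Summary of Product Characteristics, and not all of the article's text was available here. A renal provision in one of these cannot be ruled out. This also stands, and it is why a cross-reference would be an acceptable fix. It does not remove the mismatch among three statements that are all printed.

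**Renal function is looked after.** Exclusion 9 is a deliberate limit, creatinine is measured on treatment, blood counts are taken at baseline and days 7 and 14, and the Data Monitoring Committee assesses safety. These are real safeguards, but monitoring is not a basis for the dose.

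**Stronger readings a reader might infer:**

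- *The trial admits patients with severely reduced function.* That label depends on outside formulas and on age, sex and weight. Cockcroft-Gault reaches 50 mL/min at the limit, and many eligible patients with a raised creatinine would be well inside it.
- *The CRP result is biased.* Equal randomisation against placebo, analysed by intention to treat, protects the comparison within the eligible population. The Background also reports that higher doses gave no greater CRP reduction in rheumatoid arthritis.
- *Infection or neutropenia will be more frequent in these patients.* Nothing shown links renal function to exposure or to either event. The quoted rates have no renal breakdown, and the Background places neutropenia after a month or more of treatment, against 14 days here.
- *The criterion must be rewritten on eGFR.* The documents do not require this, and the choice of renal measure is clinical.

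**Conclusion.** The point holds as a mismatch between the stated dosing basis and the eligible population. Followed as written, the protocol allows 14 fixed daily doses in patients with reduced renal function for whom the available text gives no dosing basis. That conclusion needs only the three sections compared above.

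The size of the gap at its edge rests on assumed equations, ages and weights: about 18 to 33 mL/min/1.73 m² by MDRD or CKD-EPI, or 17 to 50 mL/min by Cockcroft-Gault. The documents do not say how many recruits would fall in the gap, so no effect on event rates can be calculated. The issue is patient safety and dose rationale; the validity of the primary comparison is not in question.

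**What to change.** Reconcile the IL-1ra Background section, exclusion 9 and Study treatment so that the dosing statement and the renal criterion describe the same population. If the pharmacy or product information already covers eligible patients with reduced renal function, a cross-reference from the eligibility or treatment section would be enough.

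Which passage changes, and what dose, threshold or renal measure is used, is for the sponsor's clinicians; none is proposed here. The cost is a short amendment. If the criterion is the part that changes, there may be a few fewer eligible patients. Creatinine and eGFR are already scheduled at baseline, so no new measurement is needed if either is the measure chosen.

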### Randomisation

Randomisation will be performed using a 24-hour voice interactive system set up the trial co-ordinating centre (Clinical Trials and Evaluation Unit (CTEU) of the Royal Brompton Hospital, London). Centres will be asked for a few simple details about the patient including initials, date of birth and eligibility criteria. The caller will be given a randomisation number, corresponding to blinded study treatment, and a fax or e mail will be sent to the centre confirming this. Randomisation will be stratified by centre and by whether glycoprotein IIb/IIIa antagonists are being used or planned. Patients entered into the study in this way will be considered as part of the intention to treat cohort irrespective of whether they actually receive treatment or not, or if they subsequently with draw from the study.

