#### Drug related serious adverse reactions

• Serious Infections – Previous trials conducted by Amgen demonstrated an incidence of serious infections in 1.8% of IL-1ra treated patients compared to 0.7% in placebo group. There were no on-study deaths due to serious infectious episodes.

• Neutropenia – Administration of IL-1ra was associated with neutropenia (ANC < 1.5 × 10^9^/I) in 2.4% of patients compared with 0.4% of placebo patients. None of these patients had serious infections associated with the neutropenia.

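### No exclusion for a low neutrophil count, although the protocol names neutropenia as a drug-related serious reaction and already takes a baseline full blood count

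*Protocol article*

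**What the plan says.** The Exclusion criteria section of the protocol article numbers 14 items. The only one that concerns blood cells is "11. Eosinophilia". The list does set a numerical laboratory limit elsewhere: "End stage renal disease or a Creatinine > 220" (μmol/L). The inclusion criteria contain no blood-count condition.

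Under Drug related serious adverse reactions, the protocol lists neutropenia, defined as an ANC below 1.5 × 10^9/L, "in 2.4% of patients compared with 0.4% of placebo patients". It adds: "None of these patients had serious infections associated with the neutropenia". The background section on IL-1ra gives a milder picture, "neutropaenia in <1% of patients after a month or more of treatment".

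Study related investigations and follow-up schedules a "full blood count (baseline, days 7 and 14"), with blood drawn before each dose. Table 1 starts study drug on day 1.

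**The concern.** The protocol names the hazard, gives a cut-off for it and collects the measurement, but does not use the measurement to decide who may enter. A patient who already has a low count could therefore be given daily injections of a drug that the protocol itself associates with neutropenia.

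What is at stake is the safety of a very small number of patients. The primary outcome, the sample size and the significance thresholds do not depend on it.

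**Working it through.** **1. Could another exclusion catch the patient?** Five come close:

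| Exclusion | What it removes | An isolated low neutrophil count? |
|---|---|---|
| 7, serious co-morbidity | Only patients unlikely to complete the trial | Not removed |
| 8, rheumatic, connective tissue or inflammatory bowel disease | Some patients likely to have low counts | Not removed |
| 12, anti-TNF treatment | Some patients at risk of infection | Not removed |
| 13, active infection | Infection already present | Not removed |
| 14, malignancy | Some causes of a low count | Not removed |

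These criteria remove some causes and consequences of neutropenia. None looks at the count itself, so a patient with a low count and none of these conditions remains eligible.

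**2. When would the low count next be looked for?** Study drug starts on day 1 (Table 1). Table 1 ticks the full blood count against days 1 to 7 as a block, but the text names day 7. Blood is drawn before dosing, so the doses given before that sample are those of days 1 to 6, which is 6 of the 14.

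**3. How many patients?** The protocol gives no prevalence of neutropenia at entry. I assume 0.1% to 1%. The abstract plans 186 patients, so 186 / 2 = 93 per arm.

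- Neutropenic at entry, whole trial: 186 × 0.001 = 0.19 to 186 × 0.01 = 1.86.
- Of these, allocated to IL-1ra: 93 × 0.001 = 0.09 to 93 × 0.01 = 0.93.

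**4. On-treatment neutropenia, for context only.** The safety-section rates give 93 × 0.024 = 2.2 cases on IL-1ra and 93 × 0.004 = 0.4 on placebo, if rates from earlier trials of unstated duration carried over to 14 days. The background figure of under 1% gives fewer than 93 × 0.01 = 0.93 on IL-1ra. Two weeks of dosing points to the lower end. These counts do not measure the gap, because an entry criterion would not stop a patient with a normal baseline count from becoming neutropenic later.

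**5. Would the check fit the entry process?** Exclusion 9 needs a creatinine result, exclusion 10 a pregnancy test where relevant, and exclusion 11 the patient's eosinophil status. Eosinophil status ordinarily comes from a differential white count, which also reports neutrophils. Entry already waits on laboratory results of this kind.

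**The case against.** The strongest opposing case is that nothing here is misstated or contradictory; the point asks for one more item on a long list, and the expected benefit is slight. Several parts of that case stand.

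- The entry prevalence is assumed, and the resulting number on IL-1ra is below one patient across its whole range.
- The label of serious comes from a section heading. A count just under 1.5 × 10^9/L does not by itself meet the protocol's definition of a serious event.
- Exposure is short, patients are seen often in the first week, and the background section describes neutropenia only after a month or more.
- A clinician who checks for eosinophilia would probably see the neutrophil count as well.
- Product and pharmacy guidance that is not shown might cover the matter.

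These points limit the size of the concern but do not remove it. The reassurance about infection covers patients with neutropenia in earlier company trials; the protocol does not say that any of them began treatment neutropenic. The two neutropenia figures differ, and the higher one has no stated duration, so the lower one cannot settle the question. A count that a clinician happens to see is not an entry rule. The exclusion list is printed as a numbered list and refers to the Trial Manual where it means to (cardiogenic shock), so it does not read as a summary. Whether the unseen guidance contains a neutrophil rule cannot be checked either way.

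**Conclusion.** The concern holds. As the protocol is written, an otherwise eligible patient with an isolated low neutrophil count can be randomised and dosed, with no scheduled recount until six doses have been given.

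The point is minor. Its size rests entirely on the assumed entry prevalence, and the documents give no data on outcomes in patients who start with a low count, so extra harm in them is inferred. The change is worth making because it uses a cut-off and a test that the protocol already has. It would be hard to justify if it needed new procedures.

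**What to change.** Add one exclusion: absolute neutrophil count below 1.5 × 10^9/L on the baseline full blood count. This is the protocol's own definition of neutropenia; the sponsor's clinicians may prefer another limit.

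Read the result before randomisation and confirm it at the randomisation call, which already asks for eligibility criteria. It should not be left to the interval between randomisation and first dose. Under Randomisation, every patient entered is "considered as part of the intention to treat cohort irrespective of whether they actually receive treatment or not", so a low count noticed late would leave an untreated patient in that cohort.

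The cost is one line in the list and one question at the call, with no new test. There are two downsides. The count must be back before randomisation and inside the dosing window: "The first dose of IL-1ra will be given within 24 h +2 h of the positive Troponin". There would also be a few more screen failures, about 0.2 to 1.9 per 186 patients at the assumed prevalence.

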### Study treatment

Eligible patients will be randomised in equal proportions between IL-1ra and placebo, receiving either a once daily, subcutaneous (s.c). injection of IL-1ra (dose 100 mg per 24 h) for 14 days, or a daily s.c. injection of placebo for 14 days. The hospital pharmacist will issue the relevant drug package. (Please see appendices for pharmacy information).

The study drug and placebo will be provided by Amgen Inc in its commercially available recombinant form which is in clinical use for the treatment of arthritic conditions. The study drug and placebo will be relabelled by Amgen, in collaboration with CTEU according to MHRA guidelines.

The first dose of IL-1ra will be given within 24 h +2 h of the positive Troponin. Injections will be given at a standardised time (24 ± 2 h after the previous dose), immediately after blood sampling. IL-1ra or placebo will administered to the patient by the research nurse while the patient is in hospital. During the hospital stay, the patient will be taught to self-administer the injection by the research nurse and on discharge will continue at home. This has proven possible in other ACS trials that required self injection of subcutaneous heparin [36]. Full written guidance on self injection will also be provided to patients. If self injection is found not to be possible in an individual patient for unexpected reasons, an alternative method will be sought (e.g. district nurse, or attending the hospital) to try and maintain full compliance with scheduled study drug regimen after discharge. Patients will also be asked to complete a daily injection diary. All personnel will be blinded to the identity of the syringe contents.

### Concomitant treatments and procedures

All patients will receive standardised additional treatments according to best practice including aspirin, clopidogrel, heparin (intravenous or low-molecular weight), a glycoprotein IIb/IIIa inhibitor and a statin. Other medication will be at the physicians' discretion. It is the intention that all patients will proceed to coronary angiography according to current guidelines, and subsequent revascularisation if necessary.

